# National implementation of an optimal standardised technique for right-sided colon cancer: protocol of an interventional sequential cohort study (Right study)

**DOI:** 10.1007/s10151-023-02801-6

**Published:** 2023-04-25

**Keywords:** Right-sided colon cancer, Right hemicolectomy, Minimally invasive, Laparoscopic, Robot-assisted, National implementation

## Abstract

**Purpose:**

Minimally invasive right hemicolectomy (MIRH) is the cornerstone of treatment for patients with right-sided colon cancer. This operation has evolved during recent decades, with many innovations and improvements but this has also resulted in high variability of uptake with subsequent substantial variableness. The aim of this ongoing study is to identify current surgical variations, determine the most optimal and standardised MIRH and nationally train and implement that technique to improve short-term clinical and long-term oncological outcomes.

**Methods:**

The Right study is a national multicentre prospective interventional sequential cohort study. Firstly, current local practice was evaluated. Subsequently, a standardised surgical technique for right-sided colon cancer was determined using the Delphi consensus method, and this procedure was trained during hands-on courses. The standardised MIRH will be implemented with proctoring (implementation cohort), after which the performance will be monitored (consolidation cohort). Patients who will receive a minimally invasive (extended) right hemicolectomy for cT1-3N0-2M0 colon cancer will be included. The primary outcome is patient safety reflected in the 90-day overall complication rate according to the Clavien–Dindo classification. Secondary outcomes will include intraoperative complications, 90-day mortality rate, number of resected tumour-positive lymph nodes, completeness of mesocolic excision, surgical quality score, locoregional and distant recurrence and 5-year overall survival. A total number of 1095 patients (365 per cohort) will be included.

**Discussion:**

The Right study is designed to safely implement the best surgical practice concerning patients with right-sided colon cancer aiming to standardise and improve the surgical quality of MIRH at a national level.

**Trial registration:**

ClinicalTrials.gov: NCT04889456, May 2021.

**Supplementary Information:**

The online version contains supplementary material available at 10.1007/s10151-023-02801-6.

## Background

For colon cancer located in the caecum, ascending colon, hepatic flexure or proximal transverse colon, the cornerstone of treatment is minimally invasive right hemicolectomy (MIRH). This can either be performed by conventional laparoscopy or a robot-assisted technique. The aim of right hemicolectomy is to remove the right hemicolon with tumour-free margins and an intact mesentery containing all tumour-draining lymph nodes, to restore bowel continuity, and performing this procedure with the least possible surgical trauma. The disease-specific quality of MIRH is first of all determined by the extent and completeness of the mesocolic excision including the correct plane of dissection according to oncological principles. High-quality surgery aims to provide optimal locoregional control with minimal collateral damage, and will be reflected by the patient’s short- and long-term clinical outcomes [1–3]. As observed in clinical practice and noted in the literature, the surgical procedures are carried out with a high degree of variation between surgeons and institutions. In addition the quality of surgery is variable depending on learning curves, patient factors and availability of specialised teams. This variability is of relevance to clinical and oncological outcomes, thus illustrating the need for a standardised technique.

Substantial procedural variation in MIRH for right-sided colon cancer is present [4–6]. Minimal invasive surgery has been widely adapted, but the technique has been evolving during almost 30 years [7]. In the last decade, there has been specific focus on low-pressure pneumoperitoneum, intracorporeal anastomosis, extraction site and complete mesocolic excision (CME) technique. CME encompasses a dissection along the embryological planes to create an intact envelope of mesocolic fascia with a central vascular ligation to include all the draining lymph nodes along the supplying segmental vessels [8–12]. There is a disparity between current medical practice and the recommendations from best evidence and international guidelines regarding several steps of the MIRH, and there were also considerable regional differences [6]. These resemble the reality in surgical practice due to an absence of regular training programs, and a lack or a delay of implementation is present for the majority of innovations. Standardisation and subsequent training of surgical techniques and credentialing of surgeons have been found to reduce the adjusted in-hospital mortality [13, 14]. Recently, a large cohort study demonstrated that high surgical quality is associated with a better long-term survival of patients with colorectal cancer [15].

The current ongoing study aims to educate, train and implement a standardised minimally invasive surgical technique for right-sided colon cancer according to the latest and best evidence. The primary objective is to implement the new technique safely without an increase in the 90-day postoperative complication rate, while improving long-term oncological outcomes. The secondary objective is to validate a procedure-specific competency assessment tool (CAT) for this operation and use it to assess surgical quality to demonstrate the added value of training and proctoring and to correlate surgical quality with patient-related outcomes.

## Methods

This study protocol is written in accordance with the SPIRIT guidelines [16, 17]. The SPIRIT checklist is provided in the Appendix I in the supplementary material.

### Study design

The design of this trial is a national multicentre prospective interventional sequential cohort study including 43 participating centres (Appendix II in the supplementary material). Current local practice has been prospectively evaluated (and regarded/utilised as the first, control cohort) and subsequently compared to the intervention cohorts, after implementation of the optimal standardised surgical technique during a proctoring phase and then without intervening anymore in the consolidation phase (the second and third cohort respectively). A transition period is scheduled following the control cohort, in which consensus will be reached about the standardised MIRH using the Delphi method and education and hands-on training of the standardised technique is performed, before the technique will be implemented.

### Study objectives

The primary objective of this study is to safely implement a standardised technique of MIRH without increasing the 90-day postoperative complication rate, and to ultimately improve long-term outcomes for patients with right-sided colon cancer in the Netherlands. It is hypothesized that this will translate into a reduction of local and distant disease recurrence and thereby an improved 5-year overall survival (OS) and 3-year disease-free survival (DFS).

Secondary objectives are (1) to evaluate current national surgical variations of MIRH and their impact to clinical outcomes (already finished, namely phase 1); (2) to reach consensus concerning the standardised stepwise surgical technique for MIRH using the most recent insights from literature and guidelines and using the Delphi method (already finished) [18]; (3) to design and validate a CAT for the MIRH reflecting all the steps from the Delphi consensus; (4) to evaluate the effect of training and proctoring of the standardised MIRH (comparing control, implementation and consolidation cohorts) on surgical quality and (5) on short- and long-term clinical outcomes.

### Ethical consideration

The trial will be conducted according to Good Clinical Practice guidelines and the principles of the declaration of Helsinki (2013, [19]) and in accordance with the Medical Research Involving Human Subjects Act (WMO) and other guidelines, regulations and acts. This study is approved by the Medical Ethical Committee (METC) of the Amsterdam UMC, location VUmc (2021.0273). The protocol is registered by ClinicalTrials.gov (NCT04889456).

### Study population

Eligibility criteria for study participation include (1) patients with planned laparoscopic or robot-assisted (extended) right hemicolectomy for colon cancer of the caecum, ascending colon, hepatic flexure or proximal transverse colon, (2) age above 18 years and (3) signed informed consent.

A patient will not be eligible for inclusion in case of the presence of one or more of the following exclusion criteria: (1) cT4b/multivisceral resection, (2) cTNM stage 4 (M1), (3) ASA 4, (4) immune-modulating medication, (5) prior midline or transverse laparotomy larger than 10 cm (not including Pfannenstiel and McBurney’s incision), (6) perforated disease/peritumoral abscess/fistula, (7) acute obstruction, (8) emergency surgery, (9) neuroendocrine neoplasm (NEN), (10) other primary malignancy treated within 5 years from diagnosis of colon cancer, except for curatively treated prostate, breast, skin and cervical cancer.

### Informed consent procedure

Eligible patients will be approached for entry into the study at the first outpatient visit at the surgical department. The informed consent procedure includes study explanation, a written patient information sheet and adequate time for questions before signing the study consent form prior to the surgical procedure. Written informed consent is given by the patient to a participating surgeon, resident or research nurse at the outpatient clinic. Every included patient will be assigned a four-digit study number and only the local investigation sites have access to a decryption code.

### Study outline

This study consists of five phases as is schematically displayed in Fig. 1.

**Fig. 1 Fig1:**
[figure not shown]
Schematic of the five-step approach of the Right study

*Phase 1*: the variation of current surgical techniques amongst surgeons and centres for right-sided colon cancer was evaluated by prospective inclusion of consecutive patients into the *control cohort*. The first patient was included in October 2021, and currently all patients for this phase of the study have already been included. The preoperative CT imaging, full-length surgical video, pictures of the front and the back of the specimen and clinicopathological outcomes, as well as the CT imaging 1 year postoperatively (which is part of the routine oncological follow-up regimen in the Netherlands) were collected. The patients were treated according to the surgeon’s preference of surgical technique and local hospital perioperative care protocols. In this phase, anonymised video analysis of all the cases will be performed to evaluate variability and surgical quality.

*Phase 2*: a Delphi method was applied with two colorectal surgeons from each participating institution (*n* = 43) after the inclusion period of the control cohort was closed, to establish a detailed standardised technique of MIRH for colon cancer. The consented standardised technique includes essential elements that could potentially improve outcomes such as setup, surgical approach, mesocolic plane dissection, level of vascular ligation with the extent of vertical lymphadenectomy, the technique of the anastomosis and the extraction site.

*Phase 3*: the consented standardised technique was taught to all participating colorectal surgeons (*n* = 86) during a 1-day hands-on surgical *training* course. The standardised MIRH was trained in several skills centres in the Netherlands. The same two surgeons from each participating centre who contributed in the second phase participated in this phase. The courses consisted of a theory session with several presentations about the best evidence, anatomy and the optimal standardised surgical technique, followed by a hands-on training on human cadavers in the afternoon to apply and practise the technique. All proctors of the Right study first participated in a teach the teacher MIRH CME training in the presence of ESCP faculty before training the participating surgeons.

*Phase 4*: the new standardised MIRH technique will be implemented in a controlled fashion by proctoring the surgeons of the participating centres. The same two surgeons who were trained during phase 3 will consecutively include all eligible patients. This phase is referred to as the *implementation phase* and, similar to the control cohort, the preoperative CT imaging, full-length surgical videos, pictures of the front and the back of the specimen and clinicopathological outcomes as well as the CT imaging 1 year postoperatively will be collected. A total of 11 proctors throughout the Netherlands are selected on the basis of their experience in performing MIRH and in proctoring as well. They will be physically present within the operating room the first time the standardised technique is applied, after which teleproctoring will be used for the following sessions. Teleproctoring entails monitoring of the procedure by the proctor from a distance with the means of immediate communication between proctor and surgeon. After each proctor session, an evaluation (global assessment score, GAS) form will be completed in which the surgical procedure itself will be assessed on certain points and the specimen quality is rated. In addition, on that GAS form, both the proctor and the surgeon will each decide on the necessity to proctor/be proctored again. In phase 4, prospective anonymised video analysis of all the cases will be included with feedback to participating surgeons to stimulate the learning curve and to evaluate surgical quality.

*Phase 5*, the final phase: a third consecutive group of patients will be included to observe consolidation of the standardised technique after the learning curve without proctoring (*consolidation phase*). Again, the same preoperative CT imaging, full-length surgical videos, pictures of the front and the back of the specimen and clinicopathological outcomes as well as the CT imaging 1 year postoperatively will be collected and analysed, in order to be able to compare the performance with the control cohort and implementation period. This phase will involve a prospective and anonymous video analysis of every case to assess the surgical quality.

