### Sample size calculation

The sample size calculation is based on safety with non-inferiority for the primary endpoint, the overall 90-day morbidity. In the Dutch national colon cancer audit, the overall postoperative complication rate after MIRH was 26% [22]. As all contributing hospitals within this study are represented in the national database, it can be assumed that the control cohort of the Right study has the same percentage of postoperative complications, i.e. 26%. A non-inferiority margin of 7% was defined. Therefore, introducing the new standardised technique will still be considered safe if the overall postoperative complication rate does not exceed 33%. A total of 1095 patients (365 patient in each of the three prospective cohorts) will be needed to show that there is no difference between the control and experimental (i.e. standardised surgical technique) treatment. With this number of included patients, it can be demonstrated with 80% certainty that the lower limit of the one-sided 95% confidence interval (or equivalently a 90% two-sided confidence interval) will be above the non-inferiority limit of 7%.

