### Statistical analysis

Baseline patient and procedure characteristics and perioperative outcome parameters are categorical, continuous and dichotomous variables, and will be presented accordingly. The chi-square test will be used to compare dichotomous and categorical data among patient groups. Descriptive outcomes will be reported as median with interquartile range (IQR) or mean with standard deviation (SD). According to their distribution, the Mann–Whitney *U* test will be used to evaluate intergroup variation.

Oncological outcomes will be determined using Kaplan–Meier analyses, with comparison of relevant patient groups using the log-rank test. Predictors of main outcome parameters will be determined by selecting relevant variables based on expected association with subsequent univariate analysis. Alongside the stratified comparisons as described above, multivariate analysis will be performed to determine the independent association of factors with a specific outcome parameter using logistic and Cox regression analyses. A *p* value of less than 0.05 will be considered to be statistically significant. All analyses will be performed with IBM SPSS statistics, version 23.00 (IBM Corp Amonk, NY, USA). Design of the CAT will be assessed to test reliability using generalizability theory. The outcome parameters of the CAT will be compared with clinical outcomes using univariate analysis and multivariate analysis to determine the independent association of factors with a specific outcome parameter using logistic and Cox regression analyses.

Before data is locked for analysis, the statistical analysis plan will be completed, and decisions will be made on stratification criteria, planned subgroup analysis, and how to handle baseline imbalance.

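### The named between-cohort tests and the sample size treat patients as independent, although the same 43 centres supply all three cohorts; the primary confidence interval should account for centre

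*Protocol article*

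**What the plan says.** In the protocol article, Study design gives 43 centres and three sequential cohorts. Study outline, Phase 3, gives two trained surgeons per centre, 86 in all.

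The Statistical analysis section names the chi-square test for dichotomous and categorical data, the Mann–Whitney U test, Kaplan–Meier curves with the log-rank test, and regression: "multivariate analysis will be performed to determine the independent association of factors with a specific outcome parameter using logistic and Cox regression analyses". The competency assessment tool (CAT) scores are to be related to clinical outcomes with the same regression methods. No random effect, cluster-robust error, or centre or surgeon term is mentioned. Stratification criteria, subgroups and the handling of baseline imbalance are left to the SAP; clustering is not on that list.

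The Sample size calculation takes a 26% complication rate and states "A non-inferiority margin of 7% was defined". It uses a one-sided 5% level and gives 365 patients per cohort, with which "it can be demonstrated with 80% certainty" that the margin is respected. It mentions no design effect.

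On who treats the patients, Phase 4 says "The same two surgeons who were trained during phase 3 will consecutively include all eligible patients". Phase 1 says only that current variation "was evaluated by prospective inclusion of consecutive patients into the" control cohort. Phase 5 does not say who operates.

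**The concern.** The Background section itself describes marked variation between surgeons and institutions. Outcomes within a centre, and more so within a surgeon, are then likely to be correlated. The same centres recur in every cohort, so two forces act on a between-cohort difference. Stable centre effects cancel, which makes an independence-based standard error too large. Centre effects that shift between periods do not cancel, which makes it too small. The trial changes practice in every centre, with a learning curve, so uneven shifts are plausible.

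The primary conclusion is a safety claim read off a confidence limit against a 7-point margin. An interval that is too narrow declares safety too often. For outcomes that depend mainly on the surgeon (CAT score, operative time, node count), the correlation, and hence the error, can be much larger. In the CAT–outcome regressions surgeon skill is the exposure, so repeat cases by one surgeon are not independent observations.

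**Working it through.** **Inputs from the article.** Control rate 26%, margin 7 points (so 33% is the limit), one-sided level 0.05, power 80%, 365 per cohort, 43 centres, 86 surgeons.

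**Cluster sizes.** 365/43 = 8.49 patients per centre per cohort. 365/86 = 4.24 per trained surgeon per cohort, if those surgeons treat everyone.

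**Reproducing the 365.** For control against the two later cohorts pooled (1:2), under independence:

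n = p(1−p)(1 + 1/2)(z₀.₉₅ + z₀.₈₀)² / 0.07² = 0.26 × 0.74 × 1.5 × 6.183 / 0.0049 = 364.1, rounded up to 365.

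Power at 365 v 730 is 80.1%. An equal-size comparison would need 486 per arm. The figure therefore matches a pooled 1:2 comparison of independent patients with no design effect. The pooling is inferred from the match; the article does not state it.

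**Effect of clustering on the variance.** Let m = 8.49 be patients per centre per cohort, ICC the within-centre correlation, and CAC the correlation of a centre's effects between cohorts. With every centre in every cohort (equal sizes), the true variance of the between-cohort difference divided by the independence variance is

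DE = 1 + (m−1)·ICC − m·ICC·CAC.

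The actual one-sided error of a nominal 5% test is 1 − Φ(1.645/√DE). The article gives neither ICC nor CAC, so both are assumed.

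| ICC | CAC | DE | One-sided error | Power, 365 v 730 |
|---|---|---|---|---|
| 0.02 | 1 | 0.98 | 4.8% | 80.8% |
| 0.02 | 0.8 | 1.01 | 5.1% | 79.6% |
| 0.02 | 0.5 | 1.06 | 5.6% | 77.9% |
| 0.05 | 1 | 0.95 | 4.6% | 81.8% |
| 0.05 | 0.8 | 1.03 | 5.3% | 78.9% |
| 0.05 | 0.5 | 1.16 | 6.4% | 74.7% |

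**Simulation of the primary comparison.** 43 centres, rates set to 26% in control and 33% in both later cohorts, so every declaration of non-inferiority is an error. Analysed as 730 v 365 with the independence interval. The unequal-centre column comes from 6,000 replicates and the equal-centre column from a separate run of 20,000. Centre sizes and SDs (logit scale) are assumptions.

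| Centre SD | Centre-by-period SD | Unequal centres | Equal centres |
|---|---|---|---|
| 0.5 | 0 | 5.0% | – |
| 0.3 | 0.3 | 6.5% | 5.7% |
| 0.5 | 0.3 | 7.3% | 5.5% |
| 0.5 | 0.5 | 9.4% | 7.2% |

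With centre SD 0.3 and centre-by-period SD of only 0.1–0.2, the error is 4.9–5.6%. In a further simulation the independence interval gave 4.6–9.0%, while a centre-clustered robust interval held 4.7–5.5%.

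**Surgeon-driven outcomes.** At an assumed ICC of 0.3:

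- CAC 1: DE = 1 + 7.49 × 0.3 − 8.49 × 0.3 = 0.70, so the true standard error is √0.70 = 0.84 of the stated one.
- CAC 0.5: DE = 1 + 7.49 × 0.3 − 8.49 × 0.3 × 0.5 = 1.97, so it is √1.97 = 1.40 times the stated one.

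**The case against.** **Left to the SAP.** This is a condensed article, the SAP was still to be completed, and robust errors or random effects are commonly specified there. Stratification by centre could also fall under the deferred stratification criteria. That has weight, and it is why the article should not be said to ignore centre altogether. But the article already names independence-based tests and lists what it defers, and clustering is not listed. Stratifying by centre would also remove only the stable part of the centre effect, not the part that shifts between cohorts.

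**Small for the primary endpoint.** This stands. With stable or nearly stable centres the error stays close to 5%. A reader might apply the simple design effect 1 + (m−1)·ICC, which at ICC 0.05 is 1.37 and cuts power to 68.4%. That is an upper bound, reached only if a centre's effects in different cohorts are unrelated. The article does not support it, because the same centres serve every cohort.

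**Who operated.** A reader might infer that the control cohort was operated on by a wider set of surgeons and the later cohorts by two selected ones, so that technique and surgeon selection are confounded. The article does not support this as a finding. The two-surgeon limit is written for the implementation cohort only, and it concerns who includes patients; that they also operate is an inference. Silence about control operators in a condensed article does not show that others operated, and Phase 3 counts the 86 as the full set of participating surgeons. One can calculate that a control rate 1–3 points higher because of operator mix would raise the false non-inferiority rate from 5% to about 10–27%. But that gap is assumed in size and sign, and the calculation applies it to all 730 later patients. What remains is a possibility worth checking.

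**Feasibility.** Surgeon-within-centre plus centre-by-cohort random effects would be fragile for the primary endpoint: 4.24 × 0.26 ≈ 1.1 events per surgeon per cohort. The article describes video analysis as anonymised and does not list the operating surgeon as a collected variable. Both objections stand, and the fix is limited accordingly.

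**Conclusion.** The point holds in a limited form. The between-cohort tests as named, and the sample size, assume independent patients in a design where 43 centres contribute repeatedly to three cohorts. The stated standard errors are not valid as written, but the direction of the error cannot be told from the article.

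For the primary endpoint the consequence is modest: about 5% one-sided error with stable centre effects, and about 6–9% with centre-by-period SD 0.3–0.5 and unequal centres (5.5–7.2% with equal centres). For surgeon-driven outcomes it may be material, with standard errors off by a factor of 0.84 to 1.40 at ICC 0.3. All these sizes rest on assumed ICCs, SDs and between-period correlations. That operators differed between cohorts is possible but not shown.

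**What to change.** 1. Take the primary risk difference and its 90% confidence interval from an analysis that accounts for centre: centre-clustered robust standard errors, or a centre-stratified estimate with clustered standard errors.
2. Use surgeon- or centre-clustered models for the secondary between-cohort comparisons and for the CAT–outcome regressions.
3. State who operated in each cohort. Where the operating surgeon is recorded, add a sensitivity analysis of the primary endpoint with control cases restricted to the 86 trained surgeons.

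The cost is some extra analysis work, a confidence interval that may be slightly wider, and a smaller control set in the sensitivity analysis. No further patients are called for. Items 1 and 2 can be written into the SAP before data lock using centre alone. Item 3, and any surgeon-level clustering, depend on whether the surgeon can be identified per case, which should be checked first.
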